## Abstract

**Background:**

Individuals with early phase cognitive impairment are frequently affected by existential distress, social avoidance and associated health issues (including symptoms of stress, anxiety, and depression). The demand for efficient psychological support is crucial from both an individual and a societal perspective. We have developed a novel psychological intervention (Psychological Intervention tailored for Patients with Cognitive Impairment, PIPCI) manual for providing a non-medical path to enhanced psychological health in the cognitively impaired population. The current article provides specific information on the randomized controlled trial (RCT)-design and methods. The main hypothesis is that participants receiving PIPCI will increase their psychological flexibility (the ability to notice and accept interfering thoughts, emotions, and bodily sensations without acting on them, when this serves action in line with personal values) compared to participants in the active control (cognitive training) group and the waiting list control group. The secondary hypotheses are that participants receiving PIPCI will improve psychological health (stress measures, quality of life, depression, and general health) compared to participants in the active control group and the waiting list control group.

**Materials and Methods:**

This three-arm RCT will recruit participants from the cognitive centers at Karolinska University Hospital in Stockholm and randomize approximately 120 individuals in the early phase of cognitive impairment to either an experimental group (psychological intervention once a week for 10 weeks), an active control group (cognitive training once a week for 10 weeks) or a waiting list control group. Intervention outcome will be evaluated with self-report questionnaires on physical and psychological aspects of health, cognitive assessment, biological markers (obtained from blood and saliva) and health care costs. Assessments will be performed at pre- (1 week before the interventions) and post-intervention (1 week after the interventions), as well as at a 6-month follow-up.

**Discussion:**

The development of a potentially feasible and effective psychological intervention tailored for early phase cognitive impairment (PIPCI) has the potential to advance the non-pharmacological intervention field. This is especially important given the extensive burden for many affected individuals and their families and the current lack of effective treatments. If the psychological intervention discussed here shows feasibility and efficacy, there is potential for far-reaching healthcare implications for patients with early cognitive impairment at risk of developing dementia.

**Clinical Trial Registration:**

ClinicalTrials.gov: NCT04356924. Date of registration: April 22, 2020. URL: https://clinicaltrials.gov/ct2/show/NCT04356924.

## Introduction

The burden of cognitive impairment (CI) is substantial globally. CI often hinders affected people to act independently in daily life, and the close family members often carry a large burden. A considerable societal challenge is to promote the maintenance of cognitive health in order to prevent cognitive disability in the aging population (Wallin et al., 2018). Individuals diagnosed with subjective cognitive decline (SCD, with unimpaired performance on cognitive tests) (Jessen et al., 2014), mild CI (MCI, impaired performance on cognitive tests) (Winblad et al., 2004), prodromal dementia or dementia are frequently affected by existential distress and associated health issues (such as symptoms of stress, anxiety, and depression), as well as social stigma and avoidance. The lack of efficient disease-modifying drugs has increased the interest in dementia prevention and the promotion of psychological health among those at risk/early stages of dementia. Thus, efficient psycho-social interventions are needed both from an individual- as well as a societal perspective (Wallin et al., 2018).

Adaptation to changing life circumstances is important to individuals with CI to maintain functioning and good health (Chatterji et al., 2015). Importantly, modifiable risk factors may account for approximately 35% of dementia cases (Livingston et al., 2017), and beneficial lifestyle changes hold the potential to substantially reduce the number of expected cases (Norton et al., 2014). The Finnish Geriatric Intervention Study to Prevent Cognitive Impairment and Disability (FINGER) study was the first multidomain lifestyle intervention that showed positive effects on cognitive functioning among older adults at risk of dementia (Ngandu et al., 2015). FINGER is now globally used as a prevention model, and more than 30 countries have joined the World-Wide FINGERs network. However, it is well known that adherence influences intervention efficacy, and unfortunately, adherence to lifestyle recommendations is often lower than to medication (Coley et al., 2019). Health behaviors are also generally difficult to change, and several common characteristics, including poorer cognition and depressive symptoms, may result in lower adherence to multidomain lifestyle interventions among older at-risk individuals (Coley et al., 2019). In addition, depression or depressive symptoms are common in clinical settings, potentially reaching a prevalence of over 40% for individuals with MCI, and sub-clinical depressive symptoms are associated with the increased use of healthcare (Meeks et al., 2011).

Although the demand for psychological support is significant in the cognitively impaired population, there is a lack of efficient psychological interventions to maintain and improve psychological health and to facilitate adherence to health-promoting behavioral change (Wallin et al., 2018). Cognitive training for individuals with MCI has been evaluated in a randomized controlled trial (RCT) and compared with a group intervention targeting psycho-social support using cognitive behavioral therapy (CBT) techniques (Belleville et al., 2018). Results showed that cognitive training improved the use of strategies in daily life, but neither cognitive training nor CBT improved patient mood or well-being. In addition, a systematic review stated that modified CBT approaches have shown promise in improving the quality of life in individuals with MCI and early dementia (Regan and Varanelli, 2013). However, although previous research has shown some promise, the authors call for studies with a more rigorous methodology, and larger RCT studies with better control group conditions. Thus, previous research on psychological treatments for individuals with early onset of CI with strong methodology is still limited. Increased knowledge of how to prevent, cope, and intervene with CI is therefore utterly needed, especially for those that struggle with adherence to lifestyle changes (Wallin et al., 2018).

To enhance health and functioning among individuals in an early phase of CI, we have developed a new psychological intervention. The objective of this intervention approach is to (a) improve psychological flexibility, or the ability to behave in accordance with personal values and long-term goals also in the presence of negative experiences (Wicksell et al., 2010), and (b) increase the patient’s motivation for meaningful life-style changes as defined in the FINGER concept, and for them to live their life in correspondence with personal goals. The current intervention manual is developed within the CBT tradition and takes into account the known challenges for cognitively affected individuals, and therefore for example includes additional sessions and the systematic utilization of reminders, validation techniques, repetition, and concrete examples. CBT represents a wide variety of interventions aimed at decreasing distress as well as increasing emotional, psychological, physical and social functioning (Turk et al., 1983). Recent developments within CBT, particularly acceptance and commitment therapy (ACT), emphasize the utility of acceptance and mindfulness strategies in order to facilitate value-based action when facing subjective difficulties in life that are beyond direct control, which in part stands in contrast to a number of interventions that focus on reduction or control of symptoms (Hayes et al., 2006). ACT has been empirically evaluated for a variety of psychiatric/somatic conditions, such as chronic pain and depression (Hayes, 2016). In brief, the treatment objective in ACT is to improve psychological (or behavioral) flexibility, defined as the ability to notice and accept interfering thoughts, emotions and bodily sensations without acting on them, to facilitate behavior in accordance with personal values and long-term goals also in the presence of those negative experiences (Wicksell et al., 2010). Furthermore, psychological flexibility is a key component in the change process in ACT treatment, mediating the treatment effect on pain interference, catastrophizing and anxiety (Wicksell et al., 2011; Kemani et al., 2016). ACT has also been RCT-evaluated for chronic pain by members of the current research group (Wicksell et al., 2008), and the most recent evaluation of ACT by the American Psychological Association (Division 12) was strongly supportive of ACT as treatment for “chronic or persistent pain in general” (American Psychological Association, 2010). Notably, despite the state of evidence, accessibility to CBT and ACT is low, particularly for individuals with CI such as SCD or MCI. In addition, these treatments are generally not adapted for individuals with CI. If the current intervention is effective, it has the potential to enhance psychological adjustment and health in individuals with CI. More specifically, the proposed intervention may improve the ability to adjust to the implications of cognitive decline, which potentially may also delay disease progression, and have significant health economic effects.

### Objectives and Outcomes

We will evaluate the efficacy of the psychological intervention (PIPCI) manual in an RCT comparing the intervention with both an active control group condition (cognitive training), and a waiting list control group condition. The primary objective is to evaluate intervention-related changes in psychological flexibility measured with the second version of the Acceptance and Action Questionnaire (AAQ-II) (Bond et al., 2011). The secondary objectives are to further evaluate intervention-related changes with measures of psychological health, cognitive measures and biological markers (obtained from blood and saliva). The behavioral measures will also be evaluated in relation to changes in biological markers (obtained from blood and saliva; see section “Materials and Methods” for further information). We will also evaluate how the participants experience the intervention, and how they handle preventive actions, using qualitative methods.

### Hypotheses

#### Main Hypothesis

1.The main hypothesis states that participants receiving PIPCI will increase their psychological flexibility compared to participants in the active control group and the waiting list control group and that this effect will be maintained at 6 months follow-up.

#### Secondary Hypotheses

1.The secondary hypotheses state that participants receiving PIPCI will improve psychological health (stress measures, quality of life, depression, and general health), and increase their telomerase activity compared to participants in the active control group and the waiting list control group.2.An additional secondary hypothesis state that participants receiving PIPCI, and participants in the active control group, will improve on the cognitive test measures compared to the waiting list group. However, we do not have any directed hypothesis comparing PIPCI and the active control group.

Exploratory research questions (without any directed hypotheses)

1.Can we identify significant pre-intervention predictors for intervention outcomes?2.How do participants perceive the intervention?3.Is PIPCI cost-effective and does it impact health-economic variables?

The current protocol article aims to provide a description of the conceptual model behind the novel psychological intervention manual as well as specific information on the study design, materials and methods.

## Materials and Methods

### General Design

The psychological intervention manual was developed with a developmental mixed-method according to the Medical Research Council guidance (Supplementary Material) (Moore et al., 2015). Thus, the developmental and innovative parts of the research project used an interactive design approach where both patients’ and expert clinician’s interactions are vital. The evaluation trials will be conducted according to the Standard Protocol Items: Recommendations for Interventional Trials (SPIRIT) guidelines (Chan et al., 2013) and the Consolidated Standards of Reporting Trials (CONSORT) statement (Schulz et al., 2010). The present study protocol is registered at ClinicalTrials.gov with identifier: NCT04356924 (URL: https://clinicaltrials.gov/ct2/show/NCT04356924).

### Patients

Patients will be recruited from the Cognitive Centers at the Karolinska University Hospital, Solna, and Huddinge within the Stockholm metropolitan area in Sweden, where they partake in cognitive examination [including neuropsychological assessments, anamnestic interviews, neurophysiological instrumental evaluations (such as MRI), and tests for biological markers (such as cerebrospinal fluid, CSF) etc.]. Eligible patients are individuals younger than 70 years that have been diagnosed with SCD or MCI through multidisciplinary consensus agreements according to the ICD-10 (World Health Organization, 1992), and in conjunction with consensus classification for MCI (Winblad et al., 2004). Patients that express interest in participating will be evaluated using a semi-structured interview (based on the Mini-International Neuropsychiatric Interview, MINI) (Sheehan et al., 1998), and those that fulfill the inclusion criteria are then randomized to one of the three intervention arms.

Criteria for inclusion

•<70 years.•SCD or MCI diagnosis. All cognitive MCI-subtypes are eligible.•Mild to moderate psychological symptoms that are indicated to be related to the patient’s CI. The psychological symptoms should affect the patients daily living and behavior, exemplified by avoidance behavior, social anxiety, and perceived stigmatization.•Fluency in the Swedish language.•The patients should have access to a mobile telephone to be able to receive reminders via Short Message Service (SMS).•Signed informed consent.

Criteria’s for exclusion

•Dementia diagnosis and/or occurrence of serious illness and/or injury that requires immediate investigation or treatment of another type, or which is expected to worsen in the coming year (i.e., not including dementia).•Participation in other psychological treatment over the past 6 months.•Severe psychiatric comorbidity (e.g., high suicide risk), and/or severe psychiatric disorder. This will be assessed in the MINI evaluation and during the clinical cognitive examination).•Anti-depressant medication introduced or alterations in dosage <6 months ago (i.e., un-stable dose).•Mini Mental State Examination (MMSE) score <26 and/or a Montreal Cognitive Assessment (MoCA) score <24.•Stroke or head trauma <6 months ago.•Present substance abuse diagnosis.

### Evaluation Phase

#### Randomization

The fulfillment of the inclusion and exclusion criteria will be assessed through clinical evaluations at the diagnostic team (clinicians) round. All patients eligible for study inclusion will then receive verbal and written information about the project. In the next step, patients that express interest in the project sign an informed consent and will be evaluated in a semi-structured clinical interview, the Mini International Neuropsychiatric Interview (MINI), conducted by a psychologist at the Medical Unit, Medical Psychology at Karolinska University Hospital, Stockholm, Sweden. Patients that fulfill the inclusion criteria and are considered suitable for intervention are randomized. For the randomization process, we will engage the Karolinska Trial Alliance^1^, Stockholm, Sweden, an independent professional clinical research center at Karolinska University Hospital specialized in clinical trials. Blocking will be used with each block consisting of thirty participants, this is to ensure that the number of participants will be of approximately the same size. We will use two strata, and that will be on cognitive diagnosis (SCI and MCI) and gender.

#### RCT Design and Groups

Group 1 will receive the psychological intervention (experimental group), group 2 will partake in cognitive training (active control group), and group 3 will be randomized into a waiting list control group (Figure 2). Participants need to be present for at least 75% of the intervention and complete at least 75% of the homework to be considered adherent. All evaluation assessments will be conducted by blinded assessors to the extent possible. Participants cannot be blinded to group assignment, which is typical of non-pharmacological intervention trials. However, they will not be informed of the hypotheses or of which intervention (i.e., experimental intervention and active control group intervention) was considered the experimental or control condition, to minimize expectancy effects.

•Group 1, Experimental condition: Psychological intervention (PIPCI). The intervention is an adjusted (to the cognitively impaired individual) combination of CBT and ACT, including validation strategies, and psychoeducation. One focus is to increase the patient’s internal motivation for lifestyle changes, and for them to live their life in correspondence with personal goals (see section “Introduction”). Each session includes mindfulness exercises (5–10 min per occasion) that gradually become more advanced. The psychological intervention consists of 10 sessions (55 min per occasion), once a week, where the patient meets a psychologist face-to-face (either licensed or under training to be licensed, after having worked as a psychologist for 1 year under supervision) once a week. In between sessions, patients are expected to do homework assignments related to the contiguous sessions (2 × 45 min per week). Reminders will be sent to the patient’s mobile telephone via SMS. See Table 1 for the intervention structure and content overview.

**TABLE 1 T1:** Description of the sessions in the psychological intervention.

Session	Topic	Intervention strategies
**Psychiatric evaluation and goal settings**		
Pre-intervention session	Psychiatric evaluation	Evaluation with a semi-structured interview based on MINI. After a maximum of three workdays, the patient will receive a decision of inclusion or exclusion. This part is conducted before the randomization.
1	Behavior analysis	The intervention rational is presented including a tentative functional analysis of concrete situations, cognitive processes, emotions, behaviors, strategies and short- and long-term consequences of these behaviors. Also, a first discussion is held on individual intervention goals.
**Phase 1: preparation for change**		
2	Introduction to intervention	Identification of patient specific discomfort (undesirable thoughts, feelings and bodily sensations) in different situations (antecedents [A]), and an introduction to present moment focus as a way to facilitate behavioral change.
3	Continuation of the ABC model	Continuation of session 2 with a greater focus on the behaviors (B) and consequences (C) related to the previously discussed antecedent (A) situations. The therapist focuses on emotional validation and in keeping the communication straightforward and concrete.
4	Psychoeducation	Presentation of a psychoeducative model on cognitive impairment, as well as discussions of stigma and how to more effectively handle potential guilt and shame. Also, helpful cognitive strategies are discussed with respect to the patient’s specific cognitive impairments.
**Phase 2: life values**		
5	Formulation of life values	The psychologist introduces life values as ongoing aspects of life that are highly valued, as qualities we want our lives to be about, that we want to fill our lives with, and as the type of persons we want to be. And, encourages formulation of such values in different life domains, while helping the patient to understand values as a broader concept, compared to goals.
**Phase 3: shift of perspective**		
6	The direction of life values	Introduction to strategies aimed to help the patient to deal with discomfort, while at the same time encouraging behavioral steps in a valued direction, e.g., taking steps to be more socially active.
7	Value-oriented behaviors	Further formulation and clarification of life values and introduction to the formulation of concrete value-oriented behaviors, i.e., short- and long-term goals in line with the personally formulated values.
**Phase 4: Behavioral activation, exposure, and strategies**		
8	Value-oriented behavioral activation	Exercises are presented aimed to encourage values consistent behaviors and to adopt an accepting attitude toward situational discomfort (e.g., negative thoughts and related emotions) that is not directly alterable.
9	Value-oriented behaviors and strategies	Repetition of acceptance strategies is done, to help the patient to establish situational conditions in everyday life that promote the ability to act effectively in line with life values, also in the presence of discomfort. Practice in using ACT-based problem-solving strategies is also covered.
**Phase 5: Closure**		
10	Summary and closure	A summary of the intervention is done, including reflections on closure and a discussion of questions that the patient may have. Also, a plan for relapse prevention is discussed and formulated, including the need for repetition and use of strategies to handle discomfort in the future.•Group 2, active control condition: Computer-based training tasks administered with a difficulty level adapted to patient performance. The cognitive training method that will be used targets executive control (i.e., ability to coordinate thoughts and actions in accordance with internal goals) (Miyake et al., 2000). The tasks are intended to train specific types of executive functions: “Shifting” (flexibly switching between different stimuli), “Updating” (organizing information in working memory and actively exchanging old information with new) and “Inhibition” (actively inhibiting an automatic or more dominant response). An active control group is important to include to create a placebo-like condition in addition to the waiting list condition (Van De Ven et al., 2016). It is important that the participants believe that they will improve to facilitate motivation, attention, or other factors that will increase performance as well. In addition, the active control group will receive the same amount of sessions as the experimental group, thus the active control group also consists of 10 sessions (55 min per occasion), once a week. On those occasions, the patient will meet a psychologically trained (i.e., psychology student under clinical training or with an MSc in psychology) research assistant that coaches the patients during the cognitive training. Between sessions, patients are supposed to take two walks (45 min per occasion to meaningfully match the home exercises in the experimental group). Reminders will be sent to the patient’s mobile telephone via SMS.•Group 3, waiting list condition: This group only receives regular health information that is provided after the extended cognitive examination at the Cognitive Center. After the finalization of the post-intervention evaluations, this group will be offered to participate in one of the active interventions by their preference. We will conduct additional post-intervention assessments also for those individuals in this group that accept this offer to increase the power of the intervention evaluation.

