#### RCT Assessments

Data will be collected at pre-intervention (1 week before the interventions), post-intervention (1 week after the interventions) and 6 months follow-up (Figure 1). Blinded independent psychology graduated (MSc) assistants, psychology students under clinical training, or licensed psychologists will carry out the evaluation assessments to avoid biased estimates of treatment effects. Outcome analysis will be adjusted for pre-intervention baseline. Clinical data from the patients’ extended cognitive examinations will be extracted from their patient journals and statistically modeled to predict intervention outcomes.

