### Statistical Analysis

#### Strategy for the Main and Secondary Hypotheses Analyses

The continuous longitudinal data derived from the RCT will be analyzed using appropriate growth models (e.g., LMM) that in addition to studying change at the group level also can: model change on the individual level; flexibly incorporate time-varying predictors; handle dependency for repeated observations and provide correct estimates with missing data under largely unconstrained missing data conditions (Hesser, 2015). As a default strategy we will use LMM to analyze the condition by time interaction and will follow established recommendations for model specification and reporting results (Bolger and Laurenceau, 2013). In the main analysis, we will compare intervention change between the PIPCI group and the active control group. However, we will also compare the PIPCI group and the active control group with the waiting list group. An alpha level of 0.05 and a 95% CI will be used to evaluate the main and secondary analyses. Regarding the LMM-analyses, assumptions relating to the normal distribution of residuals and homogeneity of variance will be assessed, respectively, based on visual evaluation of a histogram of model residuals, as well as by a plot of the model fitted values against the residuals from the model.

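### The main hypothesis claims a maintained 6-month effect over the waiting list, but that group is offered treatment after the post assessment, so no intact randomised untreated comparator remains at 6 months

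*Protocol article*

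**What the plan says.** The Main Hypothesis expects a gain in psychological flexibility under PIPCI, "compared to participants in the active control group and the waiting list control group and that this effect will be maintained at 6 months follow-up". The effect said to last is the one defined against both control arms.

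Under RCT Design and Groups, the description of Group 3 (waiting list condition) says: "After the finalization of the post-intervention evaluations, this group will be offered to participate in one of the active interventions by their preference". It goes on: "We will conduct additional post-intervention assessments also for those individuals in this group that accept this offer to increase the power of the intervention evaluation". The offer goes to the whole arm, it is voluntary, and PIPCI is one of the options.

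RCT Assessments separates the time points: "Data will be collected at pre-intervention (1 week before the interventions), post-intervention (1 week after the interventions) and 6 months follow-up". On the length of treatment, the Group 1 description says: "The psychological intervention consists of 10 sessions (55 min per occasion), once a week". Group 2 has the same number of weekly sessions.

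The Strategy for the Main and Secondary Hypotheses Analyses says: "In the main analysis, we will compare intervention change between the PIPCI group and the active control group". It then adds that "we will also compare the PIPCI group and the active control group with the waiting list group" and names no time point for that comparison. The Sensitivity Analyses section commits to intention to treat, with maximum likelihood applied to every available observation from randomised participants.

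**The concern.** The waiting list is a randomised untreated control only up to the post assessment. After that its members may take either active treatment, including the one under test. The hypothesis nevertheless carries the waiting-list comparison forward to 6 months, and nothing in the analysis text stops it at post. Followed literally, the intention-to-treat statement keeps observations made after the offer in the model as control data.

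A 6-month contrast with that arm would estimate immediate PIPCI against having been offered a choice of delayed treatment. If PIPCI works for those who take it late, the difference shrinks, and a fully maintained benefit could be reported as having faded. Restricting the arm to those who declined does not rescue the comparison, because they select themselves. Part of the main hypothesis therefore cannot be tested as written.

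**Working it through.** **1. Does the offer come before the 6-month visit?** Yes. It follows the post assessment, which is one week after treatment ends. A delayed course takes 10 weeks plus 1 week to its own post assessment, about 11 weeks. Six months is about 26 weeks. The text does not say where the 6 months start. If they start at the pre-intervention assessment, the shortest case, the post assessment falls at about week 1 + 10 + 1 = 12. That leaves 26 − 12 = 14 weeks, so someone who starts promptly would still finish before the visit.

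**2. The plan's own power figure.** Power Estimation and Sample Size gives 93% with 35 per group for pre-to-post AAQ-II change, PIPCI versus active control. It gives no numeric effect size, SD or correlation, so the figure can be checked only conditionally. Take a medium effect as 0.5 SD, two-sided 0.05, and the article's test-retest reliability of 0.79 to 0.81 as the pre-post correlation r. With a normal approximation, a change-score analysis (SD = √(2(1 − r))) gives 89.8% to 92.4%. A baseline-adjusted analysis (SD = √(1 − r²)) gives 92.7% to 94.6%. The 93% is plausible on these assumptions but cannot be confirmed. It concerns a contrast that this point does not touch.

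**3. Dilution of the 6-month waiting-list contrast (illustration).**

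Inputs:
- True maintained effect 0.5 SD (assumed; the article says only medium).
- 40 per arm less 15% attrition: 40 × 0.85 = 34.
- Alpha 0.05 from the article; two-sided assumed.
- r from 0.5 to 0.8 (assumed; the upper end is close to the stated reliability).
- Accepters who choose PIPCI gain its full effect; cognitive training has no AAQ-II effect (both assumed).
- Uptake a and share s of accepters choosing PIPCI: not stated, so varied.

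Formulas: diluted effect = 0.5 × (1 − a × s). Power is from a two-sample t-test on change with SD = √(2(1 − r)), which is 1.00 at r = 0.5 and 0.63 at r = 0.8.

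| Uptake a | PIPCI share s | Diluted effect | Power, r = 0.5 to 0.8 |
|---|---|---|---|
| 0 | – | 0.50 SD | 53% to 90% |
| 50% | 50% | 0.5 × (1 − 0.25) = 0.375 SD | 33% to 67% |
| 50% | 100% | 0.5 × (1 − 0.50) = 0.25 SD | 17% to 36% |
| 80% | 50% | 0.5 × (1 − 0.40) = 0.30 SD | 23% to 49% |
| 80% | 100% | 0.5 × (1 − 0.80) = 0.10 SD | 7% to 10% |

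If training also improves AAQ-II, the contrast shrinks further. If late PIPCI works less well, it shrinks less.

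**4. What stays intact.** PIPCI versus active control remains a randomised comparison at post and at 6 months, since neither arm is offered a switch. PIPCI versus waiting list, and active control versus waiting list, remain intact at post.

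**The case against.** The strongest reply is that the article names PIPCI versus active control as the main analysis and sizes the trial on that contrast from pre to post. The waiting-list comparison is an addition. This stands: the primary efficacy result is not in danger, and a reader should not infer that it is.

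Second, the offer is voluntary. A reader might conclude that no untreated participants are left at 6 months. The article does not support that, because those who decline stay untreated. What is lost is an intact randomised untreated group.

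Third, no sentence spells out a 6-month test against the waiting list, and the two figures with the flow and assessment schedule are not shown. The arm may not be assessed at 6 months at all. In that case the bias and power argument falls away, but the hypothesis still claims something for which there are no data. One could also read maintenance as a within-group statement about PIPCI. The sentence does not say so; it attaches the lasting effect to the comparison with both controls.

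Fourth, handling of data after the offer is often left to an analysis plan. Such a plan can restrict the contrast, but it cannot restore the randomised untreated control that the protocol gives up, and the hypothesis would still claim too much.

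Fifth, the near-total loss of power in the last row of the table needs high uptake and every accepter choosing PIPCI with full benefit. The article offers a choice of two treatments, so that row is an extreme, not an expectation.

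**Conclusion.** The point holds in a limited form. The 6-month part of the main hypothesis conflicts with the waiting-list offer as far as the waiting list is the comparator, and the analysis text does not resolve the conflict. If PIPCI works, a 6-month contrast with that arm is biased towards no difference. At 50% to 80% uptake the assumed 0.5 SD falls to between 0.375 and 0.10 SD, depending on what accepters choose. Those sizes rest on assumed effect, correlation, uptake and choice; the direction needs only that some participants take PIPCI late and benefit.

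A reader might extend the point to the secondary, biomarker and QALY analyses. The article does not support this as a stated error: the secondary hypotheses make no 6-month claim, and no QALY comparison with the waiting list is described. The same caution applies only if such a contrast is planned.

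This should be fixed, but it does not undermine the trial's main analysis.

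**What to change.** Reconcile the Main Hypothesis, the Group 3 description, the analysis strategy and the intention-to-treat statement:

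- Test PIPCI, and the active control, against the waiting list at the post assessment only.
- Rest the 6-month maintenance claim on PIPCI versus active control.
- Report waiting-list data collected after the offer descriptively. Alternatively, keep them in an intention-to-treat contrast that is explicitly labelled immediate versus delayed or offered treatment. State which, so that the commitment to use all randomised data is not contradicted.
- State that the additional assessments of accepters, meant to raise power, are kept apart from the randomised comparison.
- Apply the same limit to any other 6-month waiting-list contrast, if one is planned.

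The offer to the waiting list need not change. The cost is wording in the protocol, the analysis plan and the registry entry. The trial gives up a 6-month claim against no treatment, which this design cannot support.
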